### **3.1. Informed Consent Process, Recruitment and Randomisation**

Participants will be recruited within 2 days of admission into COVID-19 treatment centre. The informed consent process is presented in Appendix 1. It is based on the recently published FDA Guidance on Conduct of Clinical Trials of Medical Products during COVID-19 Public Health Emergency and will ensure compliance with both GCP regulations and infection prevention and control policy at trial sites. Before enrollment, they will be given adequate information about the trial (Appendix 2), opportunity to ask questions, and sufficient time to consider participation. Before any screening procedures, an informed consent will be obtained from each eligible subject who agrees to participate in the trial (Appendix 3). This will be conducted by the clinical co-investigator or delegated healthcare personnel on site and implemented electronically using Research Electronic Data Capture (REDCap). Allocation of participants to study arm will be randomised within each site with a ratio 1:1 based on randomisation sequences generated centrally at Obafemi Awolowo University. The model will be implemented in REDCap and will include stratification by age, gender, viral load at diagnosis and presence of relevant comorbidities.

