## 3. Study Design

This is a pilot phase 2, open label randomised controlled trial. A total of 98 patients with confirmed COVID-19 diagnosis (defined as SARS-CoV-2 polymerase chain reaction (PCR) positive nasopharyngeal swab) will be recruited from participating treatment centres. Participants will be randomised to receive either the standard of care (SOC) plus nitazoxanide for 14 days, starting from day 1 or the SOC alone for 14 days.

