| Entry vital signs                                     | X     |       |       |       |          |       |          |        |            |        |        |        |
| Eligibility confirmation                              | X     |       |       |       |          |       |          |        |            |        |        |        |
| Enrolment                                             | X     |       |       |       |          |       |          |        |            |        |        |        |
| Safety blood (10 mL)                      | X     |       |       |       |          | X     |          |        |            | X      |        |        |
| Dispense standard of care                             | X     |       |       |       |          |       |          |        |            |        |        |        |
| Randomisation                                         | X     |       |       |       |          |       |          |        |            |        |        |        |
| Dispense trial intervention (BID for 14 days)         |       | X     | X     | X     | X        | X     | X        | X      | X          | X      |        |        |
| Daily vitals, including SpO 2              |       | X     | X     | X     | X        | X     | X        | X      | X          | X      | X      | X      |
| Flu-PRO                                               |       | X     | X     | X     | X        | X     | X        | X      | X          | X      | X      | X      |
| Clinical improvement assessment                       |       | X     | X     | X     | XXX      | X     | XX       | X      | XXX        | X      | X      | X      |
| Saliva or swab collection for SARS-CoV-2  | X     |       | X     |       | X        | X     |          |        |            | X      |        | X      |
| Pharmacokinetic sampling                  |       |       | X     |       | XXX      | X     |          |        |            | XX     |        |        |
| Adverse event monitoring                              |       | X     | X     | X     | X        | X     | X        | X      | X          | X      | X      | X      |
| Study exit assessment                                 |       |       |       |       |          |       |          |        |            |        |        | X      |

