 10 mL blood draws each at baseline, day 7 and day 14 will be used to assess essential biochemical (including AST, ALT) and haematology (including XXX) safety parameters.

 Sampling schedule for SARS-CoV-2 viral load: Days 0, 2, 4, 6, 7, 14, and 28.

 Sparse PK sampling in all patients paired with saliva sample for SARS-CoV-2 viral load, as well as intensive PK sampling on days 5 and 14 in 12 selected participants.

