#### **7.1. Inclusion criteria**

- Willingness and ability to provide written informed consent.
- At least 18 and not more than 75 years of age at study entry.
- SARS-CoV-2 infection confirmed by PCR test within 2 days before randomization.
- Currently symptomatic (fever or chills, cough, myalgia, sore throat, shortness of breath, or new onset of anosmia or ageusia) and at COVID-19 isolation and treatment centre.

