## 10. Specimen Shipment and Storage

Samples will be stored at 4°C for analysis within 24 hours after collection. If a delay in testing or shipping is expected, specimens will be stored at -70°C or lower. Each swab will be placed in sterile tube containing 2-3 mL of VTM containing antifungal and antibiotic supplements. Repeated freezing and thawing of specimens will be avoided. Sterile saline will be used in the absence of VTM if samples will be stored at -70°C and analysed within 72 hours. Specimens will be packaged, shipped, and transported according to the current edition of the International Air Transport Association (IATA) Dangerous Goods Regulations .

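### Randomisation is stratified by viral load at diagnosis, but nothing guarantees that value before allocation, and Section 12 does not secure adjustment for baseline viral load instead

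*Protocol*

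**What the plan says.** **Allocation.** Protocol Section 3.1 states "Allocation of participants to study arm will be randomised within each site with a ratio 1:1", using centrally generated sequences, and adds that the model "will include stratification by age, gender, viral load at diagnosis and presence of relevant comorbidities". It does not say which test or specimen supplies the viral-load value.

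**What must be known before randomisation.** Section 7.1 asks for "SARS-CoV-2 infection confirmed by PCR test within 2 days before randomization". Section 3 describes the confirmed diagnosis as "defined as SARS-CoV-2 polymerase chain reaction (PCR) positive nasopharyngeal swab". Both are qualitative; neither asks for a Ct or a quantity.

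**When the trial first measures viral load.** Footnote 2 of Table 1 (Section 4) reads "Sampling schedule for SARS-CoV-2 viral load: Days 0, 2, 4, 6, 7, 14, and 28". Table 1 also places randomisation on Day 0, and the trial drugs start on Day 1. Section 10 says "Samples will be stored at 4°C for analysis within 24 hours after collection", with freezing if testing or shipping is delayed. Section 11 sends the assays to one named laboratory, which is not among the four recruiting centres.

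**Analysis.** Section 12 compares the PCR-negative proportions between arms and mentions no covariate. For its time-to-event analysis it fits univariable Cox models and carries into the multivariable model those covariates that reach p < 0.25. Baseline viral load is not named.

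**The concern.** A stratified allocation can be made as designed only when every stratum value has been entered. Age, sex and comorbidity are known at the bedside. Viral load is known only if a laboratory has reported it, and the protocol contains no requirement that it has.

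If some diagnostic reports say no more than positive, the field will be blank or filled inconsistently, and the intended balance on viral load will be only partly delivered. This matters more here than for the other factors: two of the three primary outcomes in Section 5 are virological, and the sample size in Section 6 is argued on time to PCR negativity.

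When balance by design is uncertain, covariate adjustment is the usual safeguard. Section 12 as written does not supply it for the viral outcomes, so the trial could rely on neither.

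**Working it through.** The protocol attaches no figure to this point, so there is none to reproduce. The check sets the provisions side by side and then sizes the gain from adjustment.

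**Step 1. Is the stratum value secured before allocation?**

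| Provision | What it delivers | Secures a Ct or quantity before allocation? |
|---|---|---|
| Section 7.1, entry criterion | A positive PCR in the 2 days before randomisation | No |
| Section 3, case definition | A positive nasopharyngeal swab | No |
| Table 1 and footnote 2 | First trial specimen on Day 0, the day of randomisation; order within the day not stated | No |
| Section 10 | Assay within 24 hours if held at 4°C, later if frozen | No; no turnaround is tied to allocation |
| Section 11 | One laboratory; Ct accepted as an indicator of copy number | No; it makes a Ct usable but does not require one at diagnosis |
| Section 18.2 | Diagnostic result and other laboratory reports kept as source documents | No; a Ct could be among them but is not requested |

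No row guarantees the value, and no row rules out that a diagnostic Ct exists.

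**Step 2. Does the analysis make up for it?**

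- PCR-negative proportions at days 7, 14 and 28: a comparison of arms with no covariate mentioned.
- Cox models: Section 12 describes these for clinical improvement. If the same approach is used for time to PCR negativity, baseline viral load enters only if it is offered as a candidate and passes the p < 0.25 screen.
- Viral load over time: Section 12 describes no separate method, so nothing there fixes an adjustment.

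Baseline viral load may therefore be absent from every analysis of the viral primary outcomes.

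**Step 3. Is a suitable covariate available?** Yes. The Table 1 row "Saliva or swab collection for SARS-CoV-2" is marked on Day 0 for all participants, and trial drugs are dispensed only from Day 1. A Day 0 value is therefore pre-dose. Unlike a stratum value, it need not be reported before allocation. Because the specimen may be saliva or swab (Section 9), its type should be carried with it.

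**Step 4. How large could the gain be?** For a continuous outcome with correlation r to the baseline value, adjustment removes a fraction r² of the residual variance and multiplies the standard error by √(1 − r²), apart from a small cost in degrees of freedom. The documents give no r; 0.3 to 0.7 is assumed.

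| r (assumed) | Variance removed, r² | Standard-error multiplier |
|---|---|---|
| 0.3 | 0.09 (9%) | √0.91 = 0.95 |
| 0.7 | 0.49 (49%) | √0.51 = 0.71 |

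This applies to viral load at a fixed time. It does not carry over directly to a PCR-negative proportion or a hazard ratio.

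**The case against.** The strongest answer is that the factor is viral load at diagnosis, not on Day 0. A diagnostic PCR is mandatory, Section 11 describes one quantitative RT-PCR for both diagnosis and quantification, and it treats Ct as a measure of copy number. The natural reading is that the diagnostic Ct fills the stratum. Section 18.2 retains laboratory reports in which a Ct could appear. This stands as a reason to think that a value will often exist; it does not make it a requirement.

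A second answer is that the source of the stratum, its cut-points and missing-value handling commonly sit in a randomisation specification or SAP, which is not shown. That is fair, and none of those details is counted as missing here. The p < 0.25 screen and the unadjusted comparison, however, are what the protocol itself states.

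A third is that a truly prognostic covariate will usually pass so lenient a screen. That is true as far as it goes, but it helps only where the Cox approach is used and viral load is offered to it. It does nothing for the comparison of proportions.

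Stronger readings are tempting and are not supported:

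- *Sites must wait, guess, or use tests that are not comparable.* The protocol never asks anyone to await the Day 0 result, and no section says that diagnostic tests come from different assays or laboratories.
- *Waiting consumes the entry windows.* The 24 hours in Section 10 is a limit on storage before analysis, not a turnaround time. The 2 days from admission in Section 3.1 govern recruitment.
- *Saliva follow-up makes a swab-based stratum unusable.* A stratum needs a pre-randomisation value, not the same specimen as follow-up.
- *Viral load is the strongest predictor of the viral outcomes.* Nothing in the documents shows this.

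**Conclusion.** The point holds in a limited form. The protocol commits to a stratification factor whose value none of its provisions guarantees before allocation, so balance on viral load is not assured. A reader might infer that the treatment comparison is biased. It is not: a noisy or missing stratum entered before allocation costs chance balance, not validity.

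The practical loss is precision, because Section 12 does not ensure that baseline viral load enters the analysis of the viral primary outcomes. The amount cannot be derived from the documents. The range of 9% to 49% of residual variance rests wholly on the assumed correlation of 0.3 to 0.7 and on a continuous outcome. The case for the change is that the covariate is already scheduled for every participant and costs almost nothing to use.

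**What to change.** **Section 12.** Add a sentence such as: *The Day 0 pre-dose viral load (or Ct), together with the Day 0 specimen type (saliva or swab), will be included as a baseline covariate in the comparisons of PCR negativity and of viral load, irrespective of its univariable p-value.* For these outcomes this replaces the unadjusted comparison and the p < 0.25 screen as the route by which viral load enters.

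**Section 3.1.** Choose one:

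- remove viral load from the strata, leaving factors known at the bedside; or
- keep it, name the Ct of the qualifying diagnostic PCR as its source, and add a level for values not available.

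**Cost.** A sentence or two and one REDCap field, with no new specimen or visit and slightly more analysis work. Dropping the factor gives up balance on viral load by design, leaving the Day 0 covariate to account for it. Keeping it preserves whatever balance the available Ct values allow, at the price of an extra stratum level.

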### **3.2. Trial Intervention**

The full prescription information for nitazoxanide tablet is presented in Appendix 4(a) and that of atazanavir/ritonavir is presented in Appendix 4(b).

#### **3.2.1. Dosing and Administration**

Participants in the intervention group will receive 1000 mg nitazoxanide (two tablets of 500 mg each) with meal two times daily (8 am and 8 pm) and one tablet of 300/100 mg atazanavir/ritonavir with meal once daily (8 pm) in addition SOC.

### **3.3. Standard of care (SOC)**

SOC will be as determined by the clinical team at the treatment centres in line with the current National Interim Guidelines for Clinical Management of COVID-19 (Appendix 5).

### **3.4. Follow-up**

The treatment duration for participants in the intervention group will be 14 days. However, follow up will continue until day 28 after study entry at the end of which all participants will exit the study. The schedule of activities during the follow up period is presented in Table 1. Participants who stop study product should continue study participation off study product with continued evaluations as per the schedule of activities. The reason for study product discontinuation should be recorded. Daily survey, vital signs and SpO2 as well as Flu-PRO questionnaire will be recorded by participant (both on paper and cloud-based forms using their mobile device while connected to the internet). SpO2 will be measured after at least 5 minutes resting in a sitting or supine position. Participants with an SpO2 below 93% will repeat the assessment 2 hours later. If the repeat assessment is still below 93%, study clinician will be alerted.

## **4. Safety Assessment**

Participants will be assessed for adverse events daily throughout study period. Each morning the attending physician will ask about the side effects commonly associated of nitazoxanide (including gastrointestinal symptoms and headaches) and any additional symptoms using a structured questionnaire. Staff at the treatment centre will further assess participants for the occurrence of new symptoms at least every six hours. Adverse events will be graded according to the NIH Division of AIDS grading scale (Appendix 6) and causality will be determined using Liverpool Causality Assessment Tool (Appendix 7). All serious adverse events, including those resulting in discontinuation of trial intervention, whether or not they are judged to be related to the trial, will be recorded as per trial schedule of follow up activities. All safety issues will be reviewed after the first 15 participants in the intervention group have completed 14 days of follow up and when any grade 3 or higher adverse event occurred in the intervention group.

**Table 1.** Schedule of Follow Up Activities

| Procedure                                             | Day 0 | Day 1 | Day 2 | Day 3 | Days 4-6 | Day 7 | Days 8-9 | Day 10 | Days 11-13 | Day 14 | Day 21 | Day 28 |
|-------------------------------------------------------|-------|-------|-------|-------|----------|-------|----------|--------|------------|--------|--------|--------|
| Informed consent                                      | X     |       |       |       |          |       |          |        |            |        |        |        |
| Demography                                            | X     |       |       |       |          |       |          |        |            |        |        |        |
| Medical history (recent and current)                  | X     |       |       |       |          |       |          |        |            |        |        |        |
| Pregnancy test (for reproductive age women)           | X     |       |       |       |          |       |          |        |            |        |        |        |
| Concomitant medications                               | X     |       |       |       |          |       |          |        |            |        |        |        |
| Physical examination                                  | X     |       |       |       |          |       |          |        |            |        |        |        |
| Entry vital signs                                     | X     |       |       |       |          |       |          |        |            |        |        |        |
| Eligibility confirmation                              | X     |       |       |       |          |       |          |        |            |        |        |        |
| Enrolment                                             | X     |       |       |       |          |       |          |        |            |        |        |        |
| Safety blood (10 mL)                      | X     |       |       |       |          | X     |          |        |            | X      |        |        |
| Dispense standard of care                             | X     |       |       |       |          |       |          |        |            |        |        |        |
| Randomisation                                         | X     |       |       |       |          |       |          |        |            |        |        |        |
| Dispense trial intervention (BID for 14 days)         |       | X     | X     | X     | X        | X     | X        | X      | X          | X      |        |        |
| Daily vitals, including SpO 2              |       | X     | X     | X     | X        | X     | X        | X      | X          | X      | X      | X      |
| Flu-PRO                                               |       | X     | X     | X     | X        | X     | X        | X      | X          | X      | X      | X      |
| Clinical improvement assessment                       |       | X     | X     | X     | XXX      | X     | XX       | X      | XXX        | X      | X      | X      |
| Saliva or swab collection for SARS-CoV-2  | X     |       | X     |       | X        | X     |          |        |            | X      |        | X      |
| Pharmacokinetic sampling                  |       |       | X     |       | XXX      | X     |          |        |            | XX     |        |        |
| Adverse event monitoring                              |       | X     | X     | X     | X        | X     | X        | X      | X          | X      | X      | X      |
| Study exit assessment                                 |       |       |       |       |          |       |          |        |            |        |        | X      |

 10 mL blood draws each at baseline, day 7 and day 14 will be used to assess essential biochemical (including AST, ALT) and haematology (including XXX) safety parameters.

 Sampling schedule for SARS-CoV-2 viral load: Days 0, 2, 4, 6, 7, 14, and 28.

 Sparse PK sampling in all patients paired with saliva sample for SARS-CoV-2 viral load, as well as intensive PK sampling on days 5 and 14 in 12 selected participants.

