| Background                | COVID-19 caused by SARS-CoV-2 is an unprecedented global public health challenge which as at 24 May 2020 has spread to over 210 countries with over 5.31 million cases including 342,000 deaths. More than 1130 clinical trials are currently ongoing in an unprecedented global search for potential therapeutics and vaccines. |
| Objectives                | The purpose of this phase 2 trial is to investigate the efficacy and safety of repurposed antiprotozoal and antiretroviral drugs, nitazoxanide and atazanavir/ritonavir, in achievement of SARS-CoV-2 PCR negativity and shorten the time to clinical improvement in patients diagnosed with moderate to severe COVID-19.        |
| Recruitment               | Individuals between 18 and 75 years old who receive a PCR positive test for COVID-19 and admitted at participating COVID-19 treatment centres will be invited to participate.                                                                                                                                                    |
| Sample Size               | 98                                                                                                                                                                                                                                                                                                                               |
| Randomisation             | For this pilot study, consenting individuals will be randomised 1:1 to receive either standard of care (SOC) alone (n = 49) or SOC plus daily trial intervention (n = 49).                                                                                                                                                       |
| Intervention              | Arm 1: SOC
Arm 2: SOC + 1000 mg nitazoxanide twice daily and 300/100 mg atazanavir/ritonavir once daily with meal for 14 days                                                                                                                                                                                                 |

ObjectivesOutcome Measures

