## 2.2. Atazanavir/ritonavir

The HIV protease inhibitor, atazanavir (boosted with ritonavir), has been shown to inhibit the major protease enzyme required for viral polyprotein processing during coronavirus replication. It also blocks pro-inflammatory cytokine production. Similar to nitazoxanide, atazanavir has been shown to achieve effective concentration pulmonary tissues at approved dose of 300 mg in combination with 100 mg of ritonavir, with even more favourable ratios when compared to *in vitro* activities generated in human cell models. Hence, it is a good candidate for drug repurposing in COVID-19. Additionally, nitazoxanide is inactivated by glucuronidation and atazanavir is a well-known inhibitor. Hence, when used in combination with nitazoxanide, atazanavir is expected to enhance nitazoxanide exposure.

Therefore, based on these considerations, the combination of nitazoxanide (taken orally at 1000 mg twice daily) and atazanavir/ritonavir (taken orally at 300/100 mg once daily) is selected as the intervention for this trial.

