All subjects experiencing AEs, whether considered associated with the use of the study medication or not, must be monitored until the symptoms subside and any clinically relevant changes in laboratory values have returned to baseline, or until there is a satisfactory explanation for the changes observed. Procedures such as surgery should not be reported as AEs. However, the medical condition for which the procedure was performed should be reported if it meets the definition of an AE. For example, an acute appendicitis that begins during the AE reporting period should be reported as the adverse event and the resulting appendectomy noted on the CRF. Planned procedures such as surgery planned prior to the subject's enrolment into the study need not be reported as AEs if these are documented as planned at the screening visit. *Clinically significant* changes in physical examination and blood safety profiles should also be recorded as AEs. Severity should be recorded and graded according to the Division of AIDS Table for Grading the Severity of Adult and Paediatric Adverse Events.

All AEs, however minor, will be documented in the CRF whether or not the Investigator concludes the event to be related to drug treatment. The AE reporting period will be from the screening visit until the subject's final study visit. In addition, any untoward event that may occur subsequent to the reporting period that the Investigator assesses as possibly, probably or definitely related to the study drug medication should also be reported as an AE. AEs may be directly observed, reported spontaneously by the subject or by questioning the subject at each study visit. All AEs should be followed up until they are resolved or the subject's participation in the study ends (i.e. until the final CRF is completed for that subject). In addition, all serious and non-serious AEs assessed by the Investigator as possibly related to the investigational medication should continue to be followed even after the subject's participation in the study is over. Such events should be followed until resolution, or until no further change can reasonably be expected. Deaths occurring

---

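### The daily adverse event enquiry names prompts for nitazoxanide only; atazanavir/ritonavir, the other part of the tested regimen, is covered by a non-specific question, so its symptomatic effects may be detected less completely

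*Protocol*

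**What the plan says.** The Trial Synopsis defines the intervention arm as "SOC + 1000 mg nitazoxanide twice daily and 300/100 mg atazanavir/ritonavir once daily with meal for 14 days". Section 2.2 closes by saying that the combination "is selected as the intervention for this trial", and the official title puts the safety of the combination alongside its efficacy.

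Section 4 describes how symptoms are elicited. "Each morning the attending physician will ask about the side effects commonly associated of nitazoxanide (including gastrointestinal symptoms and headaches"), and the sentence then continues "and any additional symptoms using a structured questionnaire". The next sentence adds a second route: "Staff at the treatment centre will further assess participants for the occurrence of new symptoms at least every six hours".

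A footnote to Table 1 schedules safety blood at baseline, day 7 and day 14, which "will be used to assess essential biochemical (including AST, ALT") and haematology parameters. Section 21 gives the general rule: "AEs may be directly observed, reported spontaneously by the subject or by questioning the subject at each study visit". It also asks for every adverse event to be documented, whatever its severity or cause.

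Section 3.2 points to prescribing information for both products. For the second one it says "that of atazanavir/ritonavir is presented in Appendix 4(b").

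**The concern.** A form that names a symptom and a form that asks whether there is anything else are two different instruments. Prompted items are generally reported more fully than items left to an open question. Here the named prompts follow one product, and the other product falls under the open question.

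At stake is how the regimen's symptom profile can be read. If few effects typical of atazanavir/ritonavir are recorded, the count could mean that they were rare or that they were asked about less specifically. Section 2.2 expects atazanavir to raise nitazoxanide exposure, so tolerability of the two together is a real question for this pilot. Symptoms not elicited during the 28 days of follow-up cannot be recovered at the analysis stage.

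**Working it through.** No arithmetic applies. The protocol states no adverse event rate by method of elicitation, so there is no figure to reproduce and none to derive. The check is to set the relevant sections side by side.

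1. **What is tested.** Synopsis, Section 2.2 and Section 3.2.1: two products, both given daily on top of standard of care.

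2. **What is prompted by name.** Section 4, first part of the sentence: common nitazoxanide effects, with gastrointestinal symptoms and headache as examples. Atazanavir/ritonavir is not mentioned.

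3. **What is asked without a name.** Section 4, second part of the same sentence: any other symptom, on the same structured questionnaire. This is an active daily question put by a physician, so the second product is covered, but not by listed items.

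4. **Other routes, and what each adds for symptoms of the second product.**
   - *Six-hourly checks (Section 4).* Frequent and tied to no drug, but no items are listed.
   - *Safety bloods (Table 1 footnote).* AST and ALT are the only analytes named. They can show laboratory changes but do not elicit symptoms.
   - *Examination findings (Section 21).* Clinically significant changes count as adverse events, but Table 1 schedules the physical examination on day 0 only.
   - *General recording rules (Section 21).* They require that whatever is found is written down. They do not add prompts.

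   Each route reduces the gap. None supplies named symptoms for atazanavir/ritonavir.

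5. **Is the asymmetry reasoned?** No reason is given. Section 2.1 sets out an adverse event profile for nitazoxanide. Section 2.2 gives none for atazanavir/ritonavir, although Section 2 makes an established safety record a criterion for choosing the drugs. Section 3 also describes the intervention as nitazoxanide alone. The Section 4 wording is consistent with text written for a one-drug trial, although the protocol does not say so.

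6. **What cannot be checked.** The questionnaire is not shown, and in the text at hand Appendix 4(b) consists of a heading and a link. How many common effects of atazanavir/ritonavir lie outside the prompted list is therefore unknown.

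**The case against.** A reader who stops at the first half of the Section 4 sentence might infer that only nitazoxanide effects are solicited and that everything else is found only if the participant volunteers it. The protocol does not support that. The same sentence has the physician ask about any other symptom, staff look for new symptoms at least every six hours, bloods are drawn three times, and Section 21 accepts events observed, reported or found on questioning. It would also go too far to say that effects of the second product are certain to be under-counted, or to put a percentage on the shortfall. Any capture rate would come from outside the protocol.

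Further points on the other side are fair:

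- The examples in Section 4 are introduced as non-exhaustive, so the finished form might already list more.
- Gastrointestinal symptoms and headache are prompted whichever product causes them, and they cover the one symptom-specific safety outcome in Section 5 (nausea, vomiting and diarrhoea).
- Serious events, discontinuations and the reviews triggered by grade 3 or higher events do not hinge on a symptom prompt.
- Section 4 speaks of participants in general, so nothing indicates that the arms are asked different questions. The planned comparison is of the whole regimen with standard of care, and no safety outcome is defined by component.

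All of this stands and limits the point. What it does not remove is that nitazoxanide is the only product named for targeted questioning, and that a catch-all may be less sensitive than a named item.

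**Conclusion.** The point holds in a narrow form. Targeted elicitation in Section 4 is uneven across the two parts of the tested regimen, and no reason is given. Symptomatic effects of atazanavir/ritonavir may be detected less completely than those of nitazoxanide. This rests on one assumption, that a listed prompt finds at least as much as an open question, and on the common effects of the second product not being wholly contained in the list already prompted. The size is unknown and cannot be obtained from the documents. No bias between the arms is shown. It is a cheap improvement to safety ascertainment, not a threat to the planned comparisons.

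**What to change.** - In Section 4, reword the sentence so that the effects asked about by name are those commonly associated with nitazoxanide and with atazanavir/ritonavir, citing Appendix 4(a) and 4(b). Keep the question about other symptoms.
- Add the common symptomatic effects listed in Appendix 4(b) as named items on the same daily form.
- State that the identical list is asked in both arms. The trial is open label, so a fixed list also leaves less to the discretion of a physician who knows the allocation.

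The change concerns a data collection form and touches no dose or clinical rule. The cost is a few added items, a slightly longer daily interview and more minor events recorded.
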